# Randomized phase III trial evaluating motivational interviewing and text interventions to optimize adherence to breast cancer endocrine therapy (Alliance A191901): the GETSET protocol

**DOI:** 10.1186/s13063-023-07672-8

**Published:** 2023-10-12

**Keywords:** Breast cancer, Endocrine therapy, Adherence, Clinical trials, Diversity, Health services research, Medical research methods

## Abstract

**Background:**

Hormone receptor-positive (HR +) breast cancer is the most common type of breast cancer in the USA but has excellent long-term outcomes in recent decades, in part due to effective oral endocrine therapy (ET). ET medications are typically prescribed for 5 to 10 years, depending on the risk of recurrence, and must be taken daily. One limiting factor to ET efficacy is nonadherence, with high-risk groups for nonadherence including younger women and Black women.

**Methods:**

The Alliance for Clinical Trials in Oncology (Alliance) trial A191901 is an ongoing, four-arm (text message reminder (TMR), motivational interviewing (MI), TMR plus MI, or enhanced usual care) randomized clinical trial that tests the efficacy and effect of two interventions (TMR and/or MI) on improved ET adherence, patient-reported outcomes (PROs), and resource use requirements among HR + breast cancer survivors. Participants are randomized in a 1:1:1:1 ratio to the four arms. With an assumed loss to follow-up of approximately 11%, we plan to recruit 1180 participants. Randomization is stratified based on age and race to ensure balance between the arms, and we oversample younger and Black women, with each group representing 30% of the study population. Participants randomized to an intervention will actively participate in the intervention for 9 months, and all participants will be followed for adherence data and PRO endpoints, through the use of the Pillsy cap medication event monitoring system and Alliance ePRO survey app (i.e., Patient Cloud). The primary analysis will compare Pillsy-measured ET adherence among study arms at 12 months.

**Discussion:**

This multisite study will not only define strategies to improve adherence to breast cancer oral therapies, but it will also potentially support strategies in large cooperative research groups that can increase delivery and tolerability of ET, involve diverse patient populations in clinical research, and engage patients effectively in interventional studies, using remote and cost-effective delivery methods.

**Trial registration:**

Clinicaltrials.gov NCT04379570. Registered on 7 May 2020.

**Supplementary Information:**

The online version contains supplementary material available at 10.1186/s13063-023-07672-8.

## Background and study rationale

Hormone receptor-positive (HR +) breast cancer is a significant public health problem, with an estimated 180,000 new cases diagnosed among women in the USA annually [1]. Survival rates for HR + breast cancer have steadily improved over the past three decades, in part, due to the introduction of adjuvant endocrine therapy (ET) in the early 1990s. Taken as a once-daily oral medication, ET has proven to be a dramatically efficacious targeted therapy, reducing 10-year risk of recurrence by 47% following 5 years of tamoxifen [2], with further incremental benefits from the newer aromatase inhibitor drugs and longer treatment courses of up to 10 years [3, 4]. Currently, the standard of care for early HR + breast cancer is to treat with ET for 5 to 10 years.

Despite its therapeutic success, nonadherence to ET is a widespread problem. Several recent studies have shown that patients struggle with both early discontinuation and suboptimal dosing, collectively termed “nonadherence” [5]. Hershman and colleagues reported that only 49% of patients in a large commercial insurance cohort took ET for the entire recommended duration at the optimal schedule [6]. In Medicaid and Medicare populations, adherence difficulties emerge even earlier with an estimated 36% nonadherent in the first year and 50% non-adherent by year four [7, 8]. ET non-adherence has been linked to significant decrements in cancer-specific and overall survival in observational studies [9, 10]. In addition, clinical trials comparing different durations of tamoxifen have shown higher recurrence rates for shorter durations of therapy [11].

Many of the factors associated with ET non-adherence are more prominent for younger and Black women and represent potential points of intervention to improve patient care. Factors associated with ET nonadherence include higher side effect burden [12, 13], lower health-related quality of life at baseline, and while taking ET [12–16], lower self-efficacy [17], and poor satisfaction with decision-making and with treatment [13, 18], all of which appear to be more prevalent issues among Black women and younger women [13, 19, 20]. Attitudes and beliefs associated with non-adherence include a woman’s belief that her risk of recurrence is low and that the risk will not change if ET is discontinued [13, 20]. Our team previously found that these beliefs are more common among Black breast cancer survivors and that adjusting for such beliefs attenuates the effect of side-effect burden on non-adherence [13]. In addition, many patients report that they forget to take ET in various situations [13, 18]. Structural factors associated with non-adherence include logistical challenges accessing refills and higher co-payments [21]; as such, longer refill intervals and Medicare Part D low-income subsidies and other copayment assistance may protect against non-adherence [13, 22].

Although modifiable factors affecting ET adherence are well-documented, few effective interventions have been reported to date to address the widespread problem of ET non-adherence in breast cancer [23]. Development of such interventions faces multiple challenges. Effective designs must address multifaceted and cumulative barriers across a wide array of unrelated domains, from forgetfulness and perceptions of risk/benefit tradeoffs to side effect concerns and self-efficacy [6, 19, 21, 24–26]. Due to the large number of patients potentially affected, and the competing demands of busy oncology clinics, feasible designs must find ways to reach patients outside the clinical encounter, and to connect with high-risk groups, including younger (< 50 years old) breast cancer survivors and Black patients. Finally, if health system stakeholders are to adopt ET adherence interventions on a large scale, data regarding the resources required to implement and value of the intervention must be provided.

Successful strategies for medication adherence in non-cancer populations may be adaptable to endocrine therapy delivery. In cardiovascular disease, multi-faceted interventions that address a variety of barriers appear to be most effective [27]. Motivational interviewing (MI), a lay counseling technique in which trained personnel help patients identify their most salient barriers, facilitators, and preferred strategies [28, 29], improves adherence in HIV and other chronic diseases and can be offered remotely [29–32]. Alternatively, interventions leveraging mobile technology through “smart” devices may offer opportunities to reach more patients remotely in an efficient manner; specifically, text message reminder (TMR) systems have been linked to improved adherence in cardiovascular disease patients [33, 34]. However, the optimal combination of remotely delivered medication support strategies for oncology patients generally, and for ET patients specifically, remains unknown.

To evaluate the optimal strategy for remote support of ET adherence, we designed the Guiding Endocrine Therapy Success through Empowerment and Technology (GET SET) trial (Alliance for Clinical Trials in Oncology [Alliance] A191901). GET SET is conducted within the National Clinical Trials Network (NCTN) in the USA, and all participating sites must be one of the following: (1) a lead academic participating site (LAPS), (2) a NCTN main member site, or (3) a member of the NCI Community Oncology Research Program (NCORP) through the Oncology Patient Enrollment Network (OPEN). Sites self-select to participate in trials, provided the institution obtains institutional review board (IRB) approval and meets all the credentialing requirements included in the specific protocol. In addition, the Alliance membership committee evaluates the site’s institutional resources for clinical trials, prior clinical research experience, patient population, prior institutional performance evaluation metrics, audit results, and other regulatory considerations. The study evaluates the impact of smartphone-based text messaging reminders and telephone-delivered motivational interviewing on ET adherence, with a prospective randomized design and sampling framework that permit full evaluation of effects in young and minority populations, as well as resource use and value. The trial leverages collaborations between the University of North Carolina at Chapel Hill, The Ohio State University, and the infrastructure of the Alliance research network, with a particular focus on network partners who engage minority and younger patients. The study opened to accrual on February 4, 2021, and as of September 15, 2023, has accrued 1024 of 1180 planned patients. In this manuscript, we outline the study design and protocol considerations of the ongoing study.

## Methods

### Objectives

Guiding Endocrine Therapy Success through Empowerment and Technology (GETSET) is a randomized controlled trial designed to test the efficacy of two interventions compared to usual care: (1) a text messaging reminder (TMR) system and (2) telephone-based motivational interviewing (MI). Patients are randomized into one of four arms: TMR, MI, combination of TMR and MI, or enhanced usual care. The primary objective is to compare adherence to oral endocrine therapy at 12 months post-enrollment among the 4 arms. Secondary and exploratory objectives will describe (1) effects of the interventions on health-related quality of life and other patient-reported outcomes, (2) costs and cost-effectiveness of the interventions and other implementation outcomes, and (3) differences in disease-free survival across arms.

### Study design

Target enrollment is 1180 patients. The study population will include both 30% Black women and 30% patients under age 50, which are both groups at high risk for non-adherence. An efficient study design will be used to compare each intervention and their combination to usual care, in terms of the following: ET adherence assessed by electronic pill cap (Aim 1), patient-reported outcomes including medication self-efficacy, health-related quality of life, cancer worry, knowledge and attitudes about ET (Aim 2), and relative resource use (cost) and value of interventions (cost-effectiveness) (Aim 3). We will also evaluate whether the intervention effects on outcomes differ by race and age. We used the SPIRIT reporting guidelines to ensure we have included all pertinent clinical trial protocol information in this manuscript [35] and have included the checklist as a supplement.

### Research ethics and dissemination

The trial protocol, template informed consent forms, participant-facing materials, and recruitment materials were reviewed and approved by the NCI Division of Cancer Prevention (DCP), Alliance for Clinical Trials in Oncology’s Cancer Control Program (CCP) protocol committee, and the NCI Central Institutional Review Board (CIRB) on May 28, 2020. The trial protocol and study activities are reviewed annually by the NCI CIRB, and progress reports are submitted annually to the NCI DCP. All subsequent protocol amendments and modifications are subject to approval from the Alliance for Clinical Trials in Oncology’s Cancer Control Program (CCP), the NCI Community Oncology Research Program (NCORP), and NCI CIRB. Protocol modifications are communicated to site research staff via memorandums from the Alliance for Clinical Trials in Oncology and via monthly site staff webinars.

The study’s data will be monitored by the Alliance Data Safety and Monitoring Board (DSMB), an NCI-approved functioning body, twice per year. The DSMB follows the Alliance Policies and Procedures for all randomized phase III trials. The DSMB will review administrative information, accrual, including accrual of Black women and according to age categories, and interim analysis results. All summary findings of the DSMB will be communicated to study investigators by the Alliance.

All participant and study-related information will be stored in secure databases with password-protected access given only to members of the trial team. All study data will be coded with a unique study identification number, assigned at registration, to maintain participant confidentiality, and will be stored separately from linking participant information. Any patient-level data shared with researchers outside of the trial team for subsequent research will limit the amount of identifiable data, in accordance with informed consent forms and HIPAA authorizations obtained for trial participation.

Adverse events beyond those related to usual care are not anticipated and, as such, are not being collected or reported to the DSMB. If participants feel distressed due to participation in this minimal-risk behavioral intervention, they may choose not to continue or finish the allocated intervention and/or speak to the site staff. Participants experiencing any physical or psychological complications related to taking endocrine therapy should discuss these concerns with their treating physician.

The final dataset is the property of Alliance for Clinical Trials in Oncology which adheres to the NCI’s requirements for data accessibility. It is anticipated that individual-level data, whether de-identified or otherwise, will be available on the National Clinical Trials Network (NCTN) Data Archive or Project Data Sphere within 15 months after publication of the primary analysis. If the desired data are not available on either of these resources, the data will be made available to individuals upon request through the Alliance website. Trial results will also be disseminated via professional meeting presentations, research publications, and the clinicaltrials.gov website, which must be approved by the Alliance publications committee. The study’s website (https://getsetstudy.org) will be used to disseminate key findings to study participants and other interested parties in layperson terms.

### Patient selection

The trial enrolls women ages 18 + years whose initial diagnosis of stage I–III, HR + , HER2-neu negative, invasive breast cancer occurred within 18 months prior to trial enrollment. Participants must have received cancer-directed surgery and completed all other planned adjuvant therapy, except breast reconstruction. However, the extent of prior adjuvant therapy is not mandated. The trial employs a new user design, meaning that eligible patients have either initiated their first ET medication within the 6 months prior to enrollment, or have received a prescription with stated intent to initiate within 6 weeks post-enrollment, and have no medical contraindications to ET (e.g., existing, or planned pregnancy). Participants are required to use a smartphone for study participation; for participants who do not have a smartphone at baseline, phones and services are provided. Because the medication event monitoring (pill cap) system and the interventions themselves were designed to measure and address adherence to a single once-daily oral drug, patients whose ongoing therapy includes additional drugs such as a CDK 4/6 inhibitor, as well as those taking endocrine therapy on nonstandard schedules (e.g., tamoxifen 10 mg twice daily), are excluded; however, premenopausal patients treated concurrently with an injected gonadotropin-releasing hormone agonist (e.g., leuprolide) are eligible.

### Site requirements

Participating sites must be a member of the NCI Central Institutional Review Board (CIRB) and accept NCI CIRB review to activate new sites. A protocol-specific training is provided to all sites prior to local study activation. The training included information regarding study protocol; key eligibility criteria; intervention activities for each study arm; study procedures for site staff specific to the Pillsy medication event monitoring system, the Medidata ePRO app, and the study-provided smartphones; and brief strategies for troubleshooting study technology. Time was provided at the end of the training for questions from site staff regarding the protocol and/or study operating procedures. All institutions are audited at least once every 36 months to assure performance standards are being met and as an educational experience for the new investigators and their staff.

### Patient registration requirements

Participants are recruited by clinical research coordinators at participating sites, including the main member and NCI Community Oncology Research Program (NCORP) network sites of the Alliance for Clinical Trials in Oncology. Local site coordinators complete informed consent procedures, assess the need for a study-provided smartphone, and collect study-required contact information for intervention administration. Following consent, site coordinators complete registration and randomization procedures via a web-based registration system, which accounts for the stratification factors: age and self-identified race. Participants are randomized in a 1:1:1:1 ratio to participate in one of the four study arms. Randomization is stratified on the basis of age, in years (< 50; ≥ 50), and race (Black women; non-Black women). Participants return to the clinic for a required, in-person baseline visit to set up the Patient Cloud (ePRO) and Pillsy smartphone applications and receive other arm-specific resources. The schedule of enrollment, interventions, and assessment can be found in Fig. 1.

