### Study interventions

All study intervention components are delivered centrally by one of the coordinating centers and delivered over a 9-month period. Participants who have not started endocrine therapy medication at the time of registration must initiate the drug within 6 weeks after randomization and begin their allocated intervention within 8 weeks after randomization. Allocated intervention may be stopped prior to completion at the patient’s request or disease progression. The study schema can be found in Fig. 2.

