**ET Medication Use:**					
Medication Understanding and Use Self-Efficacy Scale (MUSE)	8	X	X	X	X
Self-reported ET adherence and persistence	17	X	X	X	X

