### Randomization and strategic staged closure

Patients are randomized using a dynamic allocation system based on the method by Pocock and Simon [46] that continuously balances the allocation of participants across the four treatment groups and race (black vs. non-Black) and age (≥ 50 vs. < 50) stratification factors, regardless of which race and age strata remain open at the time of randomization. To avoid the algorithm being deterministic, a level of randomness is added to the algorithm such that patients are assigned to the arm that leads to more imbalance 10% of the time. Participants are consented and enrolled to the trial by local site coordinators via the Oncology Patient Enrollment Network (OPEN), a web-based registration system integrated with the regulatory and roster data as well as the lead protocol organization (LPO) registration/randomization system and the Theradex Interactive Web Response System (IWRS) which is used for retrieval of the patient registration/randomization assignment. Using these systems, participant assignment to study arms is automatically completed upon enrollment. Neither participant nor study staff are blinded to intervention allocation since this would not be feasible in a behavioral intervention. However, the primary outcome assessment is measured objectively using a medication event monitoring cap, and investigators are effectively blinded to primary endpoint data since data are collected and centrally managed externally by Alliance’s RAVE system and analysts. To achieve target numbers of patients in each race and age stratum as laid out in the statistical plan, while still accruing the overall study as quickly as possible, we use a process we describe as “strategic staged closure”. Strategic staged closure is the process of monitoring accruals according to the study’s pre-specified sub-group strata (in this case, younger Black, older Black, younger non-Black and older non-Black) and closing each stratum individually as it approaches its target accrual. The study chairs meet monthly throughout the study with the statistical team to review the pace and cumulative numbers of patients accrued in each stratum. As numbers approach the desired target for each stratum, a memorandum of impending closure is prepared for distribution to participating sites setting a date for closure estimated from the recent pace of accruals in that sub-group. We aim to notify sites of impending closure approximately 2 weeks in advance to allow any patients in active screening to consent to the study before stratum closure.

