
## Outcomes

### Primary endpoint

The primary endpoint is ET adherence at 12 months post-randomization as measured by electronic pill monitoring cap (Pillsy-reported). Patients will be labeled as adherent if the proportion of days covered by any ET medication is at or above 80% (i.e., taking ET at least 292 of 365 days). Women who do not take ET for at least 292 days will be deemed non-adherent at 12 months. The primary analysis will be based on a modified intention-to-treat population (mITT), defined as all women who signed a consent form, met the eligibility criteria, were randomized, and took ET on at least one occasion; furthermore, these women will be analyzed in the arms to which they were randomized. For the primary analysis, two comparisons will be made using two chi-squared tests: TMR-only versus enhanced usual care and MI-only versus enhanced usual care. For each comparison, statistical significance will be assessed at the 2.5% level. Should either TMR-only or MI-only arms achieve statistical significance at its allocated α-level (or accumulated unused α-levels if both achieve statistical significance), then the TMR + MI vs enhanced usual care comparison will be assessed and the unused α-level passed down and applied to determine statistical significance. In this way, the type I error rate applied to the primary family of endpoints can be controlled at the 5% level.

As a sensitivity analysis, we will assess if the intervention effects on ET adherence differ by the stratification factors of age and race. Therefore, logistic regression is planned to model the binary measure of adherence at 12 months separately for each intervention vs enhanced usual care comparison so that three separate logistic regression models will be estimated. Covariates included in each logistic regression model will be age (< 50 years; ≥ 50 year), race (Black women; non-Black women), intervention arm assignment, and the interaction terms between each stratification factor (age and race) and intervention arm assignment to ascertain whether the magnitude of the intervention effect is different across the levels of age and race. Statistical significance of the interaction terms will be assessed at the 10% level with the likelihood ratio test comparing models with and without the interaction terms.

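### The unadjusted primary tests leave out the two balancing factors and endocrine therapy (ET) status at registration; stratifying on all three would give a modest gain in efficiency

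*Protocol article*

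**What the plan says.** **Who enters.** Under Patient selection, women "have either initiated their first ET medication within the 6 months prior to enrollment, or have received a prescription with stated intent to initiate"; the second group must intend to begin no later than 6 weeks after enrolment. Study interventions attaches a rule to that group: "Participants who have not started endocrine therapy medication at the time of registration must initiate the drug within 6 weeks after randomization". ET status at registration is therefore needed to apply the protocol.

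**What is balanced.** Patient registration requirements describes a web-based system "which accounts for the stratification factors: age and self-identified race". Randomization and strategic staged closure describes a Pocock-Simon procedure that "continuously balances the allocation of participants across the four treatment groups and race" and age. No other factor is named.

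**What is analysed.** Primary endpoint states: "For the primary analysis, two comparisons will be made using two chi-squared tests", each at the 2.5% level. The combination arm is tested afterwards with the alpha passed down. The only other model given for this endpoint is a logistic regression for each comparison, containing age, race, arm and the interactions of age and race with arm. ET status is in none of these.

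**Which clock applies.** Primary endpoint sets adherence at 12 months post-randomisation as at least 292 of 365 days. Study measures starts data collection at the first cap opening recorded after activation and divides by the days in the observation period.

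**The concern.** Two groups at different points in treatment are pooled, and the variable that separates them is fixed before allocation. There are two reasons to expect it to predict the outcome.

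- Background describes nonadherence as partly early discontinuation. Women some months into ET have already passed part of that period.
- On the post-randomisation clock, a late start uses up days that the 292-day rule allows a woman to miss.

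If the status is prognostic, leaving it out costs some power and leaves the estimate open to chance imbalance in a factor that the allocation does not control. The plain test also ignores age and race, which Sample size names as risk factors for low adherence and which the allocation balances. Using the balancing factors in the analysis is ordinary good practice.

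**Working it through.** **1. The plan's own figure.** Inputs from Sample size: 69% versus 81%, two-sided alpha 0.025, power 80%. The pooled rate is 0.75.

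- Uncorrected n = [2.2414·√(2·0.75·0.25) + 0.8416·√(0.69·0.31 + 0.81·0.19)]² / 0.12² = (1.3726 + 0.5104)² / 0.0144 = 246.2, so 247.
- Continuity-corrected n = (246.2/4)·[1 + √(1 + 4/(246.2·0.12))]² = 262.6, so **263**, as stated.
- Inflation for loss: 263/0.89 = 295.5 against 295 stated, and 4 × 295 = 1180.

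The stated size reproduces. At 263 per arm the uncorrected test has 82.8% power.

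**2. The late-start arithmetic (post-randomisation clock only).** A woman starting on day 42 has 365 − 42 = 323 days left. She has used 42 of the 365 − 292 = 73 days she may miss, and needs 292/323 = 90.4% of the remainder, against 80% for a woman recorded from day 0. If observation starts at the first cap opening, this difference largely disappears.

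**3. Power with and without stratification.** The article gives neither the share already on ET nor the adherence gap between the groups, so both are assumed. The gap is set in the usual-care arm. For example, with 70% on ET and a 20-point gap, the rates are 75% and 55%, and 0.7·75 + 0.3·55 = 69. A common odds ratio is chosen so that the marginal rates are 69% and 81%. Each setting has 20,000 simulated trials of 263 per arm; neither test uses a continuity correction.

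| Share on ET | Gap (points) | Plain test | Stratified (CMH) |
|---|---|---|---|
| 50% | 10 | 82.9% | 83.0% |
| 50% | 20 | 82.7% | 84.3% |
| 50% | 30 | 82.6% | 85.9% |
| 70% | 10 | 82.8% | 83.0% |
| 70% | 20 | 83.2% | 84.3% |
| 70% | 30 | 82.8% | 86.0% |

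An independent run of 40,000 trials per setting gave 84.1-84.3% at 20 points, 86.3-86.4% at 30 points and a gain of 0.2-0.3 points at 10. A normal approximation with a constant 12-point difference gave 84.4-84.7% at 20 points. At 10 points it gave 83.0-83.1% against 82.5% unstratified, a gain of about 0.5. These figures stratify on ET status alone; any gain from age and race is not quantified.

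**4. Chance imbalance.** With q the share not yet started, the SD of the between-arm difference in q is √(2q(1−q)/263).

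- q = 0.3: √(0.42/263) = 4.0 points; 1.96 SD = 7.8 points.
- q = 0.5: √(0.50/263) = 4.4 points; 1.96 SD = 8.5 points.

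Multiplying by the gap gives the shift in the estimated arm difference: 7.8 × 0.10 = 0.8 points at the low end and 8.5 × 0.20 = 1.7 points at the high end, against a target of 12.

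**The case against.** The strongest reply is that nothing here is wrong. Randomisation balances ET status in expectation, chance imbalance is already covered by the type I error rate, and the plain test stays near 83%, above its 80% target, in every setting examined. That stands. A reader might infer that the primary test is biased or invalid, or that the allocation should have used ET status. The article supports neither inference.

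It is also fair that prognosis is inferred. The Background lists of factors linked to nonadherence do not include ET status. The direction is open too: Background reports 36% nonadherent in the first year and 50% by year four in public-insurance populations, so more time on ET need not mean better adherence over the next 12 months. A reader might take the 90% requirement as established. It holds only on the post-randomisation clock. Women already on ET can lose days on that clock as well, because the cap is handed over at a baseline visit after randomisation. Adjustment does not need the direction to be known, but it gains little if the association is weak.

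On practicalities, Table 2 plans 106 Black women under 50, about 26 per arm. If 30% of them had not started (assumed), that cell holds about 8 per arm. Cochran-Mantel-Haenszel tests tolerate sparse strata, so this does not defeat the proposal. Nor does late accrual (1024 of 1180), provided that the change is fixed before outcome data are analysed. That no section calls ET status a recorded field is a fair caution, though eligibility could not be checked without it.

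The unseen full protocol or analysis plan may add an adjusted analysis. The article does, however, list the balancing factors, the primary test and the model covariates explicitly.

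**Conclusion.** The point holds as an efficiency improvement. The stated primary tests ignore age, race and ET status at registration. The first two are balanced by the allocation, and the third is needed for eligibility and plausibly prognostic.

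Under the assumed 50-70% already on ET, stratifying on ET status is worth roughly 1 to 2 points of power at a 20-point gap and about 3 at 30 points. At 10 points it is worth close to nothing: at most about 0.3 points in simulation. It also protects against a chance shift of 0.8-1.7 points for gaps of 10-20 points. The shares and gaps are assumptions, and the article anchors neither. The sample size need not change.

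Two related matters are not settled by this. The two clocks for the 12-month endpoint need reconciling in their own right; a covariate does not do that. Nor would stratification cure any arm-related exclusion arising from the requirement that the analysed population took ET at least once.

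**What to change.** Before outcome data are analysed, amend Primary endpoint as follows.

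- For each comparison with enhanced usual care, make the primary test a Cochran-Mantel-Haenszel test stratified by age (<50, ≥50), race (Black, non-Black) and ET status at registration (already taking, not yet started). Logistic regression on the same factors with a standardised risk difference is an alternative. Leave the alpha allocation and its passing down as they are.
- Keep the unadjusted chi-squared test as a sensitivity analysis.
- Add ET status as a main effect to the three logistic models, and report its balance by arm.
- Take the status from registration. The baseline survey item "Self-reported ET adherence and persistence" is a poorer source, because the baseline visit follows randomisation.

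Allocation is untouched and no new patients are needed. The cost is a primary test that differs from the one used for the sample size, some sparse strata, and little or no gain if ET status is only weakly prognostic. Fixing it in advance matters because participants and staff are not blinded, and an adjustment chosen after results are seen would be open to challenge.
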